## Abstract

**Introduction:** Simulation-based training in transesophageal echocardiography (TEE) seems promising. However, data are limited to non-randomized or single-center studies. To assess the impact of simulation-based vs. traditional teaching on TEE knowledge and performance for medical residents in cardiology.

**Materials and Methods:** Nationwide prospective randomized multicenter study involving 43 centers throughout France allowing for the inclusion of >70% of all French cardiology residents. All cardiology residents naive from TEE will be included. Randomization with stratification by center will allocate residents to either a control group receiving theoretical knowledge by e-learning only, or to an intervention group receiving two simulation-based training sessions on a TEE simulator in addition.

**Results:** All residents will undergo both a theoretical test (0–100 points) and a practical test on a TEE simulator (0–100 points) before and 3 months after the training. Satisfaction will be assessed by a 5-points Likert scale. The primary outcomes will be to compare the scores in the final theoretical and practical tests between the two groups, 3 months after the completion of the training.

**Conclusion:** Data regarding simulation-based learning in TEE are limited to non-randomized or single-center studies. The randomized multicenter SIMULATOR study will assess the impact of simulation-based vs. traditional teaching on TEE knowledge and performance for medical residents in cardiology, and whether such an educational program should be proposed in first line for TEE teaching.

## Introduction

Excellent know-how in transthoracic (TTE) and transesophageal echocardiography (TEE) is an essential requirement for the training of cardiology residents (1–3). Although TTE is rapidly taught and practiced on patients during the cardiology residency with dedicated studies (4), TEE remains too often neglected. The reference hands-on TEE teaching may be hampered by the availability of the teacher and equipment according to trainees' working patterns, and by the procedure, which is semi-invasive by itself with the need of esophageal intubation. Simulation may be a key educational tool to improve accessibility of TEE training and to accelerate the learning curve (5).

Despite a growing interest in simulation-based training (6, 7), its accessibility remains limited in the cardiology field. In a recent international survey performed with 172 young cardiologists from 43 countries, only 48% of the participants had already participated in a simulation training, while 91% considered this teaching method as “necessary” in cardiology (8). To respond to this training demand, several teams already offer to their residents a simulation education on TEE mannequin for several years (9). In France, simulation-based teaching in cardiology has also experienced significant developments, both technologically and institutionally. Indeed, simulation-based teaching is soon to become a legal obligation in the evaluation of graduate medical students (Health Law 2022) (10). However, as of yet, no national French simulation educational program exists in cardiology. The lack of studies evaluating simulation educational programs and the cost of TEE simulator may explain the lack of national consensus.

While supervised real-life TEE experience is essential, recent studies suggested that simulation-based TEE teaching is displaying significant benefit over conventional methods (11–17). To our knowledge, all these studies were non-randomized or randomized with limited single-centre sample size (11, 12, 14, 15, 18–23).

The SIMULATOR study is designed to assess the impact of SIMULation-bAsed Training on transoesophageal echocardiOgraphy leaRning for cardiology residents comparing simulation-based vs. traditional teaching on TEE knowledge and performance in cardiology residents, in several French centres. Our hypothesis is that skills and knowledge in TEE may be enhanced by the simulation-based TEE teaching.

## Methods

### Study Population and Centers

From November 2020 to November 2021, all consecutive residents in cardiology, of all training levels (year 1–4), who have never performed a TEE alone will be included in this randomized multicenter study conducted in 43 centers throughout France. The list of participating centers allowing for the inclusion of more than 70% of all French cardiology residents is provided in Supplementary Table 1. All residents who have already performed a TEE alone will be excluded. Residents will be invited via email from their local University coordinator to participate in the study.

The study will be approved by the Ethics committee of each center and authorized by the French data protection committee (*Commission Nationale Informatique et Liberte, CNIL*). Written informed consent will be obtained from all participants. Anonymized data supporting the findings of this study will be available from the corresponding author upon reasonable request. The study will be registered before starting the recruitment of the participants, and study data and results will be added at the completion of the study. All authors and future study investigators of this study have read and approved the manuscript as written.

### Randomization

Randomization with stratification by center will be performed at the individual (resident) level in 1:1 ratio, using a computer-based software (Research Randomizer 4.0; Social Psychology Network, Middletown, USA) to assign all the residents to the traditional group or to the simulation group. The random allocation sequence will be computer-generated by the statistician ([name]) prior to the study using Stata v16.0 (StataCorp, College Station, TX, USA). Cluster-level randomization at the center level was not used for the present study, considering as minimal the risk of “contamination” of the effect of the training intervention in residents allocated in the control group.

### Study Design

Each participant will complete two different tests during the study: (1) a pre-training test before starting the educational program; and (2) a final test performed 3 months after the end of the educational program. Each of these tests will include a theoretical test and a practical test on a TEE simulator (Figure 1). Notably, the pre-test will allow for an accurate assessment of each resident's theoretical and practical level in TEE at baseline.

**Figure 1 F1:**
[figure not shown]
Flowchart of the study with schedule for training sessions and examinations in the two groups.

### Baseline Participants Characteristics

The following demographic data will be collected: age, sex, residency semester, having the national diploma in echocardiography (validation on the SIDES platform), number of TTE performed, number of TEE observed, desire for a technical specialty in cardiology (cardiovascular imaging, interventional cardiology, electrophysiology, pediatric and congenital cardiology, or no technical specialty). All participants will answer a questionnaire on their prior experience of video games in childhood or currently, defined by more than 1 hour per week, as this seemed to be associated with performance on simulation-based models in previous studies (15, 24).

### Theoretical Test

The theoretical test will include 20 video-based questions online that evaluate recognition of standard TEE views, normal anatomy and some cases of mitral regurgitation, as already described (13, 19, 22, 23). Beyond the mitral regurgitation, the presence and severity of pathology and advanced TEE skills such as quantification and haemodynamic calculations will not be assessed. The residents will be given 90 s to choose the best answer out of a multiple-choice of 5 for each question (23). These tests will be designed by the experts from the French Group of Cardiovascular imaging of the French Society of Cardiology. Each question will be scored on 5 points (5 points if all the propositions correct and 0 points if at least one error), for a total of 100 points per test.

### Practical Tests

Immediately after each theoretical test (pre-training and final tests), all participants will be asked to demonstrate 10 basic views on a TEE simulator (Table 1), as previously described (14, 15). Of note, all residents of the two groups will have a few minutes before the practical test, to familiarize themselves with the handling of the simulator, without specific training and before the probe introduction. The standardized assessment that will be used by all teachers for the TEE grading scale of each views is presented in Figure 2. For each image, residents will have a maximum of 1 min to obtain their best view. The teacher will time the duration between TEE probe introduction and obtention of the specified view judged successful by the trainee. The modified Ferrero grading scale will be used to assess the quality of achievement of the views (14, 15, 23). In this grading system, each view will be marked out of 10 points according to the quality of the view. Of these 10 points, 5 will score for imaging angle and overall clarity of the view (poor quality = 0 points, average quality = 2 points, optimal quality = 5 points); and 5 will assess the presence of all the pertinent anatomic structures in the view (−1 point per missing structure not shown, and zero point if no structure identified) (Table 1). All teachers will ask for the 10 basic views in a pre-established order. Each view will be scored on 10 points, for a total of 100 points per practical test. These examinations will be evaluated by the local teacher, a certified national echocardiography teacher. Of note, residents will not be informed of their individual performance on theoretical or practical tests to avoid additional training beyond the study for performance purposes.

**Table 1 T1:** List of basic TEE views, general anatomic structures (25, 26) and the mitral valve structures (27) that will be assessed in the study.

**Basic TEE views**	**General anatomic structures**	**Mitral valve structures**
ME 4-chamber	LA/LV/RA/RV/mitral valve	A2/P2
ME commissural view (2-chamber)	LV/Mitral valve/LA/LA appendage/circumflex artery/coronary sinus	P1/A2/P3 Antero-lateral commissure Antero-lateral muscle pillar
3-chamber	LA/LV/right coronary cusp/non-coronary cusp/mitral valve	A2/P2
ME bicaval	Interatrial septum/RA/LA/vena cava	
ME RV inflow-outflow	RV free wall/RV outflow tract/tricuspid valve	
ME aortic valve SAX	Right coronary, left coronary and non-coronary cusps/pulmonary valve/tricuspid valve/inter atrial septum	
Descending aorta SAX	Descending aorta/inferior wall/superior wall	
Descending aorta LAX	Descending aorta/round shape/wall (without interruption)	
ME ascending aorta SAX	Superior vena cava/ascending aorta/aortic valve/pulmonary artery	
ME ascending aorta LAX	Right pulmonary artery/ascending aorta/aortic valve	

*LA, left atrium; LAX, long axis; LV, left ventricle; ME, midesophageal; RA, right atrium; RV, right ventricle; SAX, short axis; TEE, transesophageal echocardiography*.

**Figure 2 F2:**
[figure not shown]
Ten basic TEE views for the practical test with anatomic structures assessed. AV, aortic valve; LAX, long axis; ME, midesophageal; RV, right ventricle; SAX, short axis; TEE, transesophageal echocardiography.

### Traditional and Simulation-Based Training

After the pre-training test, all participants will complete the following training sessions corresponding to the randomization. The first group (“traditional group”) will take part in a traditional didactic training using e-learning with the free-access online course *on the SIDES-NG platform* (website: https://www.uness.fr/plateformes-sides/sides-ng). This internet-based resource was developed by the French Group of Cardiovascular of the French Society of Cardiology and is freely accessible online. No session on TEE simulator will have to be performed during the study. The second group (“simulation group”) will access online courses too. Additionally, they will receive two one-on-one teaching sessions using a TEE simulator. The teaching program will be designed to facilitate sequential TEE examination according to ESC guidelines (3). The simulation session will involve standardized initial teaching of normal cardiac, including anatomy of mitral valve with some mitral regurgitation cases, aortic valve, tricuspid valve, interatrial septum, and left atrial appendage, and demonstration of image acquisition by the teacher (time duration: 30 min) (25). The duration of each session will be 2 h with a 6:1 instructor to student ratio. Each subject will have a dedicated 20 min of hands-on to manipulate the probe and undertake a sequential TEE examination under the supervision of the teacher. Instruction and feedback will be primarily verbal, but physical assistance with probe movement will also be provided to obtain and optimize the 10 basic views. Other participants can watch their colleagues working on the TEE simulator. The time allocated on TEE simulator will be divided between the acquisition of basic views and normal cardiac anatomy, including anatomy of mitral valve, aortic valve, tricuspid valve, interatrial septum, and left atrial appendage (first session), and an in-depth learning of mitral valve anatomy in TEE using some cases of mitral regurgitation (second session). The two practical sessions will be taught by the same instructor in each center. The maximum time between the two sessions will be 2 months.

Three months after completion of the study, all participants will be invited to a final test to assess long-term retention. Participants will be asked not to access additional learning resources about TEE between the pre- and final tests. All participants in both groups will be allowed to perform TEE during their daily clinical practice throughout the study. They will have to quantify prospectively the number of TEE observed or performed after training using a personal logbook provided by the teacher.

### TEE Simulator Protocol

For the “simulation group,” the same mannequin-based TEE simulators will be used for the study (“U/S Mentor Simulator,” 3D Systems-Simbionix, Littleton, USA). Functionalities of TEE simulators have been described previously (13). All trainers of the study are certified teachers in echocardiography and are accustomed to use simulation as a teaching method. To standardize the training and the practical test on TEE simulator, all trainers will follow a webinar of 30 min presenting the entire content of each session and the final test. Eighteen simulators will be used for this study. Some University centers already have their own simulator and will perform the study without additional cost. For the other centers which do not have a simulator, we will be able to set up a system of delivery of the simulator on the other centers during a limited period allowing to carry out the study.

### Satisfaction Assessment

After completion of the two training sessions, the participant satisfaction will be assessed by an anonymous questionnaire on the quality and effectiveness of the TEE training received during this study for the simulation group. As already published (15, 19), the questionnaire will include six statements on different aspects of the training such as (1) overall satisfaction and usefulness; (2) perceived benefit; (3) duration of the sessions; (4) relevance of the current level of training; (5) ideas of improvement; and (6) whether the participants would recommend this educational program for others. Satisfaction will be assessed using a 5-point Likert scale from 1 = strongly disagree to 5 = strongly agree. Responses will be deemed negative (Likert scale 1 and 2), neutral (Likert scale 3), or positive (Likert scale 4 and 5). The satisfaction of each participant will be scored on a total of 30 points.

### Outcomes

The coprimary outcomes of the study to compare the two groups will be the scores in the final theoretical and practical tests after the training will be completed.

The secondary outcomes will be the change in theoretical and practical tests scores from pre- to final-training. In addition, we will assess the satisfaction of participants.

### Statistical Analysis

#### Sample Size Calculation

Based on recent available literature (13, 15, 19, 21) and considering normalized 0–100 points score ranges for the two co-primary outcomes, a minimally important difference of 5 points (standard deviation 7 points) will be considered for the difference in change from pre- to post-training scores in theoretical and practical tests between the two randomized groups. Under these assumptions, a sample size of 50 subjects per group (for an overall population of 100 participants) will provide 90% power to detect a statistically significant difference between the two groups at a significance level of alpha = 2.5%, applying a Bonferroni correction to account for multiple testing of the two co-primary outcomes.

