#### Statistical Methods

Demographic characteristics (age, sex, residency semester), having the national diploma in echocardiography, number of TTE performed, number of TEE observed, desire for a technical specialty in Cardiology collected at the time of randomization, will be summarized and compared between participants of the “traditional group” and the “simulation group.” Continuous data will be reported as means ± standard deviation (SD) for normally distributed data or as medians and interquartile range (IQR) for non-normally distributed data, as assessed through graphical methods and the use of the Shapiro-Wilk test for normality. Categorical data will be reported as counts and percentages. Between-groups comparisons will be performed using Student's *t*-test or Mann–Whitney test for continuous variables and using the Chi-2 or Fisher's exact test for categorical variables, as appropriate. Regarding the co-primary outcomes, on-parametric approaches (i.e., Mann-Whitney tests) will be favored over parametric tests due to the skewed distribution of test scores previously described in the literature (15). For within-groups comparisons (pre- vs. final tests), paired *t*-tests and Wilcoxon signed-rank tests will be performed for continuous variables. Longitudinal analysis of the evolution of the co-primary outcomes over the two time points (pre- and 3-month follow-up) will rely on mixed effects linear regression modeling, accounting for the correlation between repeated data over time. To address this risk of bias due the difference of number of TEE observed between the residents, an adjustment for the number of TEE observed will be performed in the final analysis. Prespecified subgroup analyses will be performed after stratifying by prior experience of video games in childhood or currently. A two-tailed *p* < 0.025 will be considered statistically significant for the primary analyses, and a two-tailed *p* < 0.05 for all other comparisons. All data will be analyzed using the *R* software, version 3.6.3 (R Project for Statistical Computing, R Foundation, Vienna, Austria) and Stata v16.0 (StataCorp, College Station, TX, USA).

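### Plain Bonferroni for the two co-primary outcomes is valid, but Holm would keep the same 5% family-wise error and give more power for the second outcome at no cost in participants

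*Protocol article*

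**What the plan says.** The Outcomes section names two co-primary outcomes: "The coprimary outcomes of the study to compare the two groups will be the scores in the final theoretical and practical tests". The Sample Size Calculation assumes "a minimally important difference of 5 points (standard deviation 7 points"). With 50 residents in each arm, 100 in all, it claims 90% power at the 2.5% level. The reason it gives for that level is multiplicity: "applying a Bonferroni correction to account for multiple testing of the two co-primary outcomes".

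Statistical Methods turns this into the decision rule: "A two-tailed *p* < 0.025 will be considered statistically significant for the primary analyses". The two sections agree. Neither describes a step-down or any passing of alpha from one outcome to the other, and no reason is given for preferring the single-step form. The article does not say whether a positive trial needs one co-primary outcome or both. The Introduction gives a general hypothesis that covers both skills and knowledge.

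**The concern.** With two hypotheses, Holm's first step is the Bonferroni step: the smaller p-value is compared with 0.025. If it is significant, only one hypothesis is left and it can be tested at the full 0.05. The family-wise error stays at 5% under any dependence between the outcomes. Single-step Bonferroni leaves that second-step alpha unused.

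The two procedures differ in one situation only: one score has p below 0.025 and the other has p from 0.025 up to 0.05. The plan calls the second score negative; Holm calls it positive at the same family-wise error. That situation is plausible here. Both groups receive the e-learning and only the intervention group has simulator sessions, so the practical effect may well be larger than the theoretical one. The conclusion about knowledge could then turn on which of two equally valid rules was written down.

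**Working it through.** **Inputs.** From the Sample Size Calculation: difference 5, SD 7, 50 per group, alpha 0.025. From Statistical Methods: two-sided test. From Randomization: 1:1 allocation. Not given: the correlation (rho) between the two test statistics, so I assume a range of 0 to 0.8. Both outcomes are given the same true effect, as in the plan.

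**1. The plan's own figure.** The standard error of the difference is 7 × √(2/50) = 1.40, so the expected z is 5/1.40 = 3.571.
- Normal approximation: Φ(3.571 − 2.241) = 90.8% at 0.025 and Φ(3.571 − 1.960) = 94.6% at 0.05.
- t-test: 90.0% at 0.025 and 94.3% at 0.05. The t-test needs 49.9 per group for 90% power, that is, 50.

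The stated 90% reproduces as power for each outcome separately.

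**2. Both outcomes confirmed, independent outcomes, t-test.**
- Bonferroni: P(both p < 0.025) = 0.9004² = 0.811.
- Holm: P(both p < 0.05) minus P(both p between 0.025 and 0.05) = 0.9425² − (0.9425 − 0.9004)² = 0.8883 − 0.0018 = 0.887.

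**3. The same with correlated outcomes, normal approximation, 50 per group.**

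| rho | Both, Bonferroni | Both, Holm | Gain (points) | At least one (either rule) |
|---|---|---|---|---|
| 0 | 82.5% | 89.4% | 6.9 | 99.2% |
| 0.3 | 83.5% | 89.8% | 6.3 | 98.1% |
| 0.5 | 84.5% | 90.3% | 5.8 | 97.1% |
| 0.8 | 86.7% | 91.3% | 4.6 | 94.9% |

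Power for each outcome taken singly rises from 90.8% under Bonferroni to between 93.1% (rho 0.8) and 94.3% (rho 0) under Holm.

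**4. Error control, by simulation.** With no effect on either outcome, the chance of any false positive is the same under both rules: 4.95% at rho 0 and 4.66% at rho 0.5. With a full effect on one outcome and none on the other, Holm's error on the null outcome is 4.8% (rho 0) or 4.6% (rho 0.5), within 5%.

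**5. What the gain is worth in participants.** On the normal approximation, Bonferroni needs about 58 per group instead of 50 to reach Holm's joint figure: 89.4% at rho 0 and 90.5% at rho 0.5.

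**6. Unequal effects (my assumption: 5 points on one outcome, 3 on the other).** The chance of confirming both rises from 42–46% to 54–57% across rho 0 to 0.8.

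**7. Dependence on the number enrolled (difference 5, SD 7, independent outcomes).**

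| Per group | Gain in joint power, normal | Gain in joint power, t-test |
|---|---|---|
| 50 | 6.9 points | 7.6 points |
| 60 | 4.2 points | 4.6 points |
| 75 | 1.7 points | 1.9 points |
| 100 | 0.3 points | 0.3 points |

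**The case against.** The strongest reply is that nothing is wrong. The method, the threshold and the sample size agree with one another, Bonferroni controls the error, and the promised 90% is delivered. That stands in full. A reader might infer from the joint figures of 81–87% that the trial is underpowered or that its 90% is misstated. The article does not support this: it powers each outcome at 2.5% and nowhere requires both to succeed. The hypothesis about skills and knowledge in the Introduction is a general aim, not a both-must-win rule. Measured per outcome, the gain is only about 2 to 3.5 points, and for at least one success it is nil.

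Second, the size of the gain is tied to 100 participants. The article gives 100 as sufficient for 90% power, not as a cap, and it plans to include all eligible consecutive residents at 43 centres. If enrolment runs well past 100, the gain at the assumed effect largely disappears, as step 7 shows. This also stands. It reduces the benefit but is no argument for the single-step rule, because Holm is never worse.

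Third, the inputs are not exactly those of the planned test. The 5 and 7 describe a difference in change scores, while the co-primary outcomes are final scores to be compared by a Mann-Whitney test. Under normal data that test would have about 88.5% power per outcome at 0.025. The percentages are therefore approximate, but the direction does not depend on them.

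Fourth, Bonferroni keeps tests and simple simultaneous 97.5% intervals aligned. This is a genuine advantage, and it is lost in exactly the cases where Holm changes the result. The article does not give it as a reason.

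**Conclusion.** The point holds as a cheap, optional improvement. The fixed 0.025 rule is valid and consistently stated, but Holm dominates it: same 5% family-wise error under any correlation, every Bonferroni rejection kept, and a positive result available for a second outcome with p between 0.025 and 0.05. At difference 5, SD 7 and 50 per group, joint confirmation rises from about 81–87% to about 89–91%. The low ends are the t-test with independent outcomes; the high ends are the normal approximation at rho 0.8. These figures assume that both true effects equal the minimally important difference, and they take the article's change-score SD for both outcomes. Dominance itself needs none of these assumptions; only the size does.

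**What to change.** In Statistical Methods, replace the fixed threshold for the primary analyses with a sentence such as:

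> Holm procedure: the smaller of the two p-values is tested at 0.025 and, if significant, the larger at 0.05 (two-sided).

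Name Holm instead of Bonferroni in the Sample Size Calculation. The 50 per group and the 90% power can stay, because 0.025 is the first-step level. The change must be fixed before any unblinded analysis.

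It needs no extra participants or data. Its one downside should be stated in the plan: if 97.5% intervals are reported for both outcomes, the interval may include zero for an outcome declared significant at the second step.
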